**Fig 1 pone.0294237.g001:**
[figure not shown]
Participant involvement in The Wellbeing Program.

## Data management plan

This project is being conducted in compliance with the HREC study protocol, Good Clinical Practice guidelines, and the HREC application regulatory requirements. All research team members recruiting and/or delivering the sessions, have completed Good Clinical Practice training and follow a Standard Operating Procedures (SOP) document that was developed by the project investigators to provide steps and processes to undertake the project. In addition, researchers have appointed an Independent Auditor who is a Registered Psychologist to monitor the project, conduct regulatory inspections, have direct access to source data/documents to ensure quality control of data and review project safety procedures.

To ensure quality and accuracy of data, all data will be collected, de-identified and stored by the research team. All study data will be collected and managed using REDCap electronic data capture tools hosted at the Telethon Kids Institute (TKI) [51, 52]. REDCap is a secure, web-based software platform designed to support data capture for research studies. All questionnaires except for the SDQ have received permission by the authors and/or owners to replicate them onto REDCap as a survey. For simplicity, each age group will have a separate survey with all age-appropriate questionnaires and will be sent to participants via email. Once participants have completed the questionnaire, they will be scored by a member of the research team. If participant scores are of concern or reach a clinical threshold, the participant will be referred for appropriate clinical psychological or medical follow up with a General Practice practitioner. Although we have received permission to replicate the CBCL and YSR in REDCap as a survey, all participant responses will be manually entered and verified in the ASEBA Web platform to generate participant scores and reports. To ensure compliance with SDQ’s copyright policy, a separate link will be sent to participants from the SDQ online platform in which scores and reports will be generated. All SDQ scores will be manually entered on REDCap by a member of the research team. All other questionnaires will be manually scored on REDCap.

To protect the participants privacy and to maintain confidentiality, data will be anonymised by allocating a participant with a unique person identification code. Raw data collected during the intervention will be securely kept on password protected computers at TKI in a project specific database that only research team members have access to. All entries will be checked by two research assistants. Upon completion, only completely anonymised measurement data and group statistics (i.e., Confidence Intervals, mean, median, range etc.) will be made available to other researchers and reported in publications. Lastly, the TKI research team and the PCH burns research team meet once a week to ensure transparency of project planning and maintain standardised procedures across both centres.

## Data preparation and statistical analysis

All screening measures will be thoroughly checked by two research members to ensure all applicable questions have been answered. Missing data will be imputed where necessary, with the method depending on attrition rates and the degree of missing data. Scoring of all screening measures will be completed in REDCap or on the measure’s online software through syntax, which will minimise the risk of data entry errors. The quantitative data will be analysed using Stata data analysis software to determine relationships between our mental health measures and significant independent variables such as demographics (e.g., birth sex, age, age at injury) and injury characteristics (e.g., nature of the burn, size, and location) using basic descriptive analyses (Objective 1). This software will also be used to determine if the measures provide meaningful information on whether our intervention improves the mental health of children and young people who have survived a burn injury. Improvements in child and caregiver mental health (via SDQ, CBCL, YSR, STAI, STAI-CH, CPSS-5, PCL-5, PSS-10, PSS and CD-RISC) pre- (T^1^) and post-intervention (T^2^, T^3^, T^4^) will be investigated (Objective 2). Normality of all data will first be tested using Shapiro-Wilk’s test, which is ideal for sample sizes of less than 50 [76]. We will also utilize graphical presentation of the data (e.g., boxplots and histograms) to aid in determination of normality in the data [76]. If the data is normally distributed, then dependent t-tests will be employed to determine change in measure scores (e.g., changes in anxiety scores). If the data is not normally distributed, then we will employ the Wilcoxon signed-rank test instead.

Individual-based Change Statistics (IBC) such as the Standardized Individual Difference or the Reliable Change Index will also be used, as these have been shown to be effective in detecting change in clinical populations and do not require arbitrary cut-off points [77]. Additionally, we will analyse the feasibility and acceptability of the intervention via adherence and compliance to the program, attrition rates and uptake of recruitment and post-session ratings (children aged 13–17 years only). Pilot feasibility studies are able to provide information on consent rates, treatment compliance and methods of outcome measurement to assess the potential efficacy of a novel intervention [78]. The results of the analysis will enable the research team to identify participant behaviour and attitude changes, improvements in mental health, and determine if our intervention design is suitable for a future roll-out [47]. Data cleaning and statistical analyses will be performed in Stata/SPSS [79].

We intend to use restriction of enrolment and statistical analyses methods to control for confounding factors. Due to the preventative and non-clinical nature of this intervention, it was imperative that we incorporated screening measures and methods which would exclude young people and/or their carers who have existing mental health concerns. Furthermore, we intend to apply correction methods (e.g., stratification by age group) as needed to further delineate the effects of the intervention based on other participant characteristics.

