### Stage 2: Intervention

#### Participants

*Participant eligibility criteria*. Eligibility will include school aged children aged 6–17 years who have sustained a burn injury and attended the Stan Perron Centre of Excellence for Childhood Burns at PCH in the previous 12 months, and their caregivers. Participants must be fluent in speaking and reading the English language (due to limited funding for interpreters and translators, alongside a lack of validated measures for other languages). Participants must also have access to an internet connected device (e.g., computer, tablet, mobile phone) to facilitate the intervention sessions and study surveys.

*Exclusion criteria*. Children aged 0–5 years will be excluded from the study as sessions for children aged 0–5 would be a family intervention involving the caregiver, rather than a child-directed intervention. Children presenting with an intentional burn injury (i.e., burn injuries that are self-inflicted or inflicted by others to cause harm [38]), or who have a diagnosed cognitive impairment (e.g., traumatic brain injury) that means they are unable to attend/understand the intervention content will be excluded from this study. Caregivers who have a known substance abuse issue or are unable to appropriately engage in the intervention due to pre-existing severe psychological distress will also be excluded. The exclusion criteria will be identified during the screening process, through discussions with the clinical and PCH burns research team and recorded patient medical notes on the Burns Information Management System (BIMS). If not previously disclosed, this information can also be identified in the demographic questionnaire provided to participants during the baseline screening process. Levels of understanding of the requirements for research participation will be determined by the completion of the consent process.

*Recruitment and consent*. Participants will be recruited by a member of the research team at their outpatient burns clinic appointment at PCH. Convenience sampling will be used to recruit participants into this pilot study from PCH due to its paediatric burn’s outpatient clinic’s proximity and accessibility for the research team. PCH oversees the management of most paediatric burn cases across WA, especially for more severe cases.

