### Instruments

During baseline assessment (T^1^), a demographic questionnaire will be administered to adolescents (12–17 years old) and all caregivers to capture their age, gender, and any mental health conditions they or their child have been diagnosed with prior to and after the child’s burn injury. For children aged 11 years and younger, caregivers will capture this information on their behalf. The potential effects and feasibility of our intervention will be assessed via the selection of measures from the screening procedure with the aim of determining whether the current content of the intervention can cause change in mental health outcomes for participants [47]. Children aged 8–17 years (self-report) and caregivers (caregiver report and self-report) will complete a range of screening tools at pre- and post-intervention (T^1^ and T^2^ respectively), as well as at 6- and 12-months post-intervention (T^3^ and T^4^ respectively), which will be used as outcome measures of the intervention and to assess mental health (Table 2).

**Table 2 pone.0294237.t002:** Child and caregiver screening measures used in The Wellbeing Program.

Construct	Measure	Participants age range	Reliability	Items (number and response procedure)	Additional information
**Internalising and externalising behaviours**	The Strengths and Difficulties Questionnaire (SDQ) [53].	Caregiver report: On behalf of children aged 6–17 years Self-report: Children aged 11–17 years only	Test-retest reliability rho = .62 and internal consistency α = .73	25 items	The SDQ is a screening tool that can be used as a treatment outcome measure for children and adolescents [53]. The SDQ asks about attributes such as emotional symptoms (5 items), conduct problems (5 items), hyperactivity or inattention (5 items), peer relationship problems (5 items) and prosocial behaviour (5 items) [53].

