Due to age range restrictions of the selected questionnaires, children aged 6–7 years old will not need to complete any self-reported questionnaires therefore, only caregiver reports will be collected for this age range. The selected questionnaires show mixed reliability among the younger age groups and often relied on parental or researcher administration to show success which is not always logistically possible [48–50]. To ameliorate this limitation, and to complement the self-reported measure, all caregivers of children in this study will be required to complete The Strengths and Difficulties Questionnaire (SDQ) and Child Behaviour Checklist (CBCL) that asks questions and statements about their child (caregiver report). Our previous research has highlighted how paediatric burns can be inherently traumatic for caregivers, particularly mothers, and thus can adversely affect their mental health outcomes [21]. Therefore, parental screening measures are included in this study despite children and adolescents being the primary target of this intervention.

All outcome measures, excluding the SDQ, will be completed at all four timepoints (T^1^, T^2^, T^3^, T^4^) and will take approximately 30–60 minutes to complete at each timepoint. The SDQ will be completed only at T^1^, T^3^ and T^4^ timepoints as the online version of the SDQ asks responders to recall information from the “previous six months”. The SDQ will be completed on the SDQ online survey platform, and all remaining measures will be completed online via REDCap [51, 52]. Permission to use the measures has been granted by the authors and/or owners. All screening measures will be administered by a research team member under the supervision of a Child and Adolescent Psychiatrist and have received training in all the data collection and analysis procedures.

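### The SDQ is listed for a T1–T2 comparison it cannot supply, and its six-month recall makes the baseline partly a pre-burn score for children burned less than six months earlier

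*Protocol article*

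**What the plan says.** Under Data preparation and statistical analysis, the plan for Objective 2 names ten measures together: "Improvements in child and caregiver mental health (via SDQ, CBCL, YSR, STAI, STAI-CH, CPSS-5, PCL-5, PSS-10, PSS and CD-RISC"). It then sets the comparison for all of them as "pre- (T^1^) and post-intervention (T^2^, T^3^, T^4^) will be investigated (Objective 2"). Change is tested by a paired t-test or the Wilcoxon signed-rank test, and individual change statistics are added.

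Under Instruments, the schedule is different for one measure: "All outcome measures, excluding the SDQ, will be completed at all four timepoints", and "The SDQ will be completed only at T^1^, T^3^ and T^4^ timepoints". The reason given is that "the online version of the SDQ asks responders to recall information from the “previous six months". No other SDQ version is named for T1. The same section has T3 and T4 at 6 and 12 months after the intervention. Children aged 6–7 complete no self-report, so their child outcomes are the caregiver-reported SDQ and CBCL.

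Under Participants, eligibility covers children aged 6–17 "who have sustained a burn injury and attended the Stan Perron Centre of Excellence for Childhood Burns at PCH in the previous 12 months". No minimum time since the burn is set. Safety considerations describes the injury in this population as recent. The burn date is among the items requested from medical records (Recruitment and consent).

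**The concern.** There are two separate problems.

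First, the analysis sentence promises a T1–T2 comparison for a measure that is not collected at T2. At ages 6–7 this leaves the CBCL as the only child outcome for the immediate pre-post contrast, and the analysis section does not show it.

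Second, a six-month recall window can reach back before the burn. The protocol takes the recall period into account when it drops T2, but says nothing about what it does to the T1 score; the limitations do not mention it either. If a child enters soon after the injury, much of the period the caregiver or adolescent is asked about at T1 lies before the burn, while the T3 and T4 periods lie after it. A change score from T1 to T3 is then partly a comparison of life before the burn with life after it, and not only of the post-burn state before and after the programme. For children burned longer ago, the same score is a comparison within the post-burn period. A pooled mean change, or a reliable change index applied to everyone, puts the two together.

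**Working it through.** The plan gives no figure on this point, so there is none to reproduce. Two checks were made.

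**Check 1: schedule against analysis**

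| Measure | Collected at (Instruments) | Contrasts listed (analysis section) | Contrasts possible |
|---|---|---|---|
| SDQ | T1, T3, T4 | T1–T2, T1–T3, T1–T4 | T1–T3, T1–T4 |
| Other nine measures | T1, T2, T3, T4 | T1–T2, T1–T3, T1–T4 | all three |

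At ages 6–7 the child outcomes are the CBCL at T2, and the CBCL and SDQ at T3 and T4.

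**Check 2: how much of the T1 window is pre-burn**

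Inputs: recall period 6 months (Instruments); time from burn to T1, k months, with no minimum (Participants); T3 six months and T4 twelve months after the intervention (Instruments).

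Pre-burn share of the T1 window = max(0, (6 − k)/6).

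| k (months) | Calculation | Share |
|---|---|---|
| 1 | 5/6 | 83% |
| 2 | 4/6 | 67% |
| 3 | 3/6 | 50% |
| 4 | 2/6 | 33% |
| 5 | 1/6 | 17% |
| 6 or more | 0 | 0% |

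If T3 falls six months after the intervention ends, as planned, its window begins no earlier than the end of the intervention. It is therefore wholly post-burn, and so is the window at T4.

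The documents give no distribution of k, so the average share has to be assumed. For k uniform on 0 to M months:

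- M = 12: half the children (about 20 of 40) have some pre-burn time in the window. The mean share over all children is (1/12) × ∫₀⁶ (6 − k)/6 dk = 3/12 = 25%, and 50% among those affected.
- M = 6: all children are affected; mean share 3/6 = 50%.
- M = 3: all children are affected; mean share (1/3) × (3 − 9/12) = 2.25/3 = 75%.

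For M of 6 or more the mean share is 3/M, so it falls if burns older than 12 months are eligible. That is possible, because the 12-month limit may qualify only the clinic attendance and not the burn.

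These are shares of calendar time. They are not SDQ points, and the documents give nothing from which an effect on the score could be derived.

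**The case against.** The strongest reply has four parts.

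- **The T2 mismatch is already settled in the text.** Instruments makes the SDQ exception explicit and gives the reason, and the analysis sentence is a collective one. With no T2 SDQ data, no wrong analysis can follow. This stands: the first problem is a wording correction and alters no result. A reader might also infer that the CBCL is the only pre-post measure of any kind at ages 6–7. The documents do not support that, because they count T3 and T4 as post-intervention and the SDQ is collected at both.
- **The recall rule was applied consistently for its purpose.** Objective 2 compares before with after the intervention. A T2 window would reach well back before the programme, whereas the T1 window lies wholly before it and the T3 window wholly after it. This also stands, so the T1 issue is not an inconsistency in the schedule. It remains a limit on what the SDQ change means, because the burn falls inside some T1 windows and outside others.
- **The direction of bias is not shown.** A reader might infer that the SDQ change is biased against the programme. This would follow if functioning before the burn was better, which the background makes plausible: it reports anxiety disorder in 28% of children with burns against 6.9% of uninjured children. T1 would then understate post-burn difficulties, and improvement would be understated. That figure compares two groups of children, however, and no pre-burn SDQ level is reported. In a single-arm study, natural recovery after a recent burn would also push the observed change the other way.
- **The stakes are limited.** The SDQ is one of ten measures, none named as primary, in a pilot that says it does not evaluate efficacy. The plan already allows stratification as needed. This limits the weight of the point, but the stratification is not tied to time since burn, and nothing tells the analyst that the SDQ baseline needs it.

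**Conclusion.** The point holds in two parts of unequal weight. The T1–T2 SDQ contrast is listed but cannot be computed; this is minor. The six-month recall makes the T1 SDQ partly a pre-burn score for every child less than six months from the burn, while T3 and T4 are wholly post-burn, so the pooled SDQ change mixes two kinds of baseline. This affects interpretation and deserves a change to the plan.

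The size depends on time since burn, which the documents do not give. On the assumed uniform distributions the mean pre-burn share of the window lies between 25% and 75%, and it would be below 25% if older burns come in. The conclusion also assumes that the six-month version of the SDQ is used at T1 and that T3 is completed on schedule.

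One further inference would go too far: that only children at least six months from burn give an interpretable SDQ result. Setting the others aside would remove the recently injured children whom the study is meant to serve. Their SDQ change can be reported, provided it is not described as change from a post-burn baseline.

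**What to change.** 1. In the analysis section, state that SDQ change is assessed from T1 to T3 and from T1 to T4 only. Note that the CBCL is the only child outcome for T1–T2 at ages 6–7, and that the SDQ serves that age group at T3 and T4.
2. Keep the pooled SDQ result. Add a descriptive report of SDQ change by time since burn at T1, under six months and six months or more, using the burn date already requested from medical records. Report the distribution of time since burn, so that the reader can see how many children are affected.
3. State that SDQ change in the group under six months is not to be read as change from a post-burn baseline, and add a sentence on T1 recall to the limitations.

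The cost is some wording and one split of an existing table; no new data are needed. The drawback is small groups. With 20% attrition, 40 × 0.8 = 32 children remain, or about 16 in each group if time since burn is uniform over 0–12 months. There will be fewer for the self-reported SDQ, which is limited to ages 11–17. The split should therefore be descriptive, with no subgroup tests.

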## Dissemination

The findings from this study will be presented at relevant research conferences, local and national research symposiums, and seminars in collaboration with our research partners (TKI, CAHS, Fiona Wood Foundation and University of Western Australia) and other medical health services. Furthermore, dissemination of the overall findings will be communicated via a published peer reviewed academic journal. Additionally, a lay summary of the outcome of the intervention after the 12-month follow up (T^4^) will be distributed to all study participants and relevant interest groups via social media platforms.

### Status and timeline of the study

Recruitment and data collection of stage 1 occurred between February and May 2022. An HREC amendment for stage 2 was approved in September 2022 and recruitment began in November 2022. Recruitment is expected to continue until November 2023 therefore, the intervention sessions will conclude in December of 2023. Given the follow-up timepoints (T^3^ and T^4^), data collection will continue until December of 2024. Data analysis will start after all T^2^ data has been collected.

## Discussion

### Summary

The purpose of this study is to evaluate the potential effects of a resilience based mental health recovery program (The Wellbeing Program) for children and adolescents who have sustained an acute burn injury. Study results will assist in informing children, their families, and clinicians about the importance and benefits of an individualised treatment to improve psychosocial recovery following a burn injury. Several aspects of the pilot data will inform the design of the larger roll-out of this intervention within the PCH burns unit and the wider community in Western Australia. The measures will be evaluated by the research team to determine if they provide meaningful information on whether the intervention improves the mental health and resilience of children and young people who have sustained a burn injury. Furthermore, the virtual format of the sessions will provide valuable insights into the acceptability of the medium, participant engagement, and feasibility of this medium as an alternative method for offering psychological, which may improve service provision for rural and remote patients.

Stage 1 of this study resulted in a co-designed intervention that incorporated feedback from community stakeholders (adolescents, caregivers) and clinicians. The recommendations that fit within the study scope were integrated into the project and further suggestions will be considered for future intervention development.

